# Intravenous immunoglobulin and rituximab versus placebo treatment of antibody-associated psychosis: study protocol of a randomised phase IIa double-blinded placebo-controlled trial (SINAPPS2)

**DOI:** 10.1186/s13063-019-3336-1

**Published:** 2019-06-07

## Abstract

**Background:**

Evidence is conflicting about a causal role of inflammation in psychosis and, specifically, regarding antibodies binding to neuronal membrane targets, especially N-methyl-D-aspartate receptors. NMDAR, LGI1 and GABA-A antibodies were found more prevalent in people with psychosis than in healthy controls. We aim to test whether these antibodies are pathogenic and may cause isolated psychosis. The SINAPPS2 phase IIa double-blinded randomised controlled trial will test the efficacy and safety of immunoglobulin and rituximab treatment versus placebo for patients with acute psychosis symptoms as added to psychiatric standard of care.

**Methods:**

We will screen approximately 2500 adult patients with acute psychosis to identify 160 with antibody-positive psychosis without co-existing neurological disease and recruit about 80 eligible participants to the trial in the period from September 2017 to September 2021 across the UK. Eligible patients will be randomised 1:1 either to intravenous immunoglobulin (IVIG) followed by rituximab or to placebo infusions of 1% albumin followed by 0.9% sodium chloride, respectively. To detect a time-to-symptomatic-recovery hazard ratio of 0.322 with a power of 80%, 56 participants are needed to complete the trial, allowing for up to 12 participants to drop out of each group.

Eligible patients will be randomised and assessed at baseline within 4 weeks of their eligibility confirmation. The treatment will start with IVIG or 1% albumin placebo infusions over 2–4 consecutive days no later than 7 days from baseline. It will continue 4–5 weeks later with a rituximab or sodium chloride placebo infusion and will end 2–3 weeks after this with another rituximab or placebo infusion. The primary outcome is the time to symptomatic recovery defined as symptomatic remission sustained for at least 6 months on the following Positive and Negative Syndrome Scale items: P1, P2, P3, N1, N4, N6, G5 and G9. Participants will be followed for 12 months from the first day of treatment or, where sustained remission begins after the first 6 months, for an additional minimum of 6 months to assess later response.

**Discussion:**

The SINAPPS2 trial aims to test whether immunotherapy is efficacious and safe in psychosis associated with anti-neuronal membrane antibodies.

**Trial registration:**

ISRCTN, 11177045. Registered on 2 May 2017.

EudraCT, 2016-000118-31. Registered on 22 November 2016. ClinicalTrials.gov, NCT03194815. Registered on 21 June 2017.

**Electronic supplementary material:**

The online version of this article (10.1186/s13063-019-3336-1) contains supplementary material, which is available to authorized users.

## Background

It is broadly accepted that psychosis and schizophrenia are caused by genetic and environmental factors, associated with excess mesolimbic and mesocortical dopamine and the *N*-methyl-d-aspartate receptor (NMDAR) hypofunction [1]. However, a range of cell surface protein and immune genetic loci are associated with schizophrenia [1, 2] and there is increasing evidence for a role of inflammation in psychosis and schizophrenia [3, 4]. Antibodies binding to neuronal or glial membrane targets, especially NMDA receptors, in the brain were first described in 2007 causing encephalopathy, with psychiatric features in over two thirds that responded to immunotherapy [5]. In such patients, isolated psychotic episodes occur in 23/571 (4%), either at presentation (5/571) or at relapse (18/571) [6].

Open-label experience from several hundred patients suggests that immunotherapy is effective in the full-blown syndrome of encephalopathy associated with anti-NMDAR antibodies [7]. Antibodies to the NMDAR or the voltage-gated potassium channel complex (VGKC) were found in 3 (7%) out of 46 patients with first-episode psychosis, without other signs of encephalitis [8]. In a prevalence study (PPiP1) we replicated previous findings as 20 (8.8%) of 228 study participants with first-episode psychosis possessed these antibodies, with a rate of 4% in healthy controls [9]. The presence of NMDAR, of leucine-rich, glioma inactivated 1 (LGI1) and of gamma-aminobutyric acid type A (GABA-A) receptor antibodies in patients with a first episode of psychosis was found to be greater then in healthy controls. We found no cases of α-amino-3-hydroxy-5- methyl-4-isoxazolepropionic acid receptor antibodies (AMPAR), a greater rate of contactin-associated protein 2 (CASPR2) antibodies in controls than patients with psychosis, and no difference in VGKC antibodies between groups [9]. The VGKC antibody radioimmunoassay is no longer recommended clinically due to non-specificity [10]. Others have found NMDAR and LGI1 antibodies in cases and controls at a low rate [11]. The antibodies were, however, found in neurological and healthy controls (e.g. 13 of 56 NMDAR antibody-positive patients in a Cambridge and University College London (UCL) study had antibodies thought to be clinically irrelevant) [12].

There is considerable evidence that anti-NMDAR antibodies are usually pathogenic, down-regulating NMDAR currents both in vitro and in vivo [13–15]. The hypothesis underlying the SINAPPS2 trial is that these antibodies are pathogenic and may be responsible for isolated psychosis.

We have recently reported on 18 patients with NMDAR antibodies, nine of whom self-resolved or responded to antipsychotics. The remaining nine patients were resistant to up to three antipsychotics, so we treated them with corticosteroids combined with either plasma exchange (PLEX) or intravenous immunoglobulin (IVIG) to good effect, resulting in reduced serum antibody level, symptomatic remission and lowered disability in the majority of patients treated, with maintenance therapy for a few patients (mycophenolate or rituximab) [16].

We conducted an uncontrolled feasibility study (SINAPPS1) to test the referral pathway and acceptability of IVIG and PLEX with corticosteroids [17]. Nine (90%) out of 10 recruited participants with acute psychosis and the presence of anti-neuronal membrane antibody (antibody-associated psychosis) received immunotherapy within 14 days from the decision to treat at two acute hospitals in England. Four participants received IVIG and six were given plasmapheresis (combined with steroids in four patients). All participants were taking antipsychotic medication as prescribed by their psychiatrists. No adverse events were reported during the treatment. The severity of psychosis symptoms and the functioning of all participants improved within two months of the last treatment session. Symptomatic improvement was remarkable in participants with NMDAR antibodies and moderate in participants with VGKC or GABA-A antibodies. The SINAPPS1 trial has confirmed the feasibility of rapid and safe provision of immunotherapy in patients with psychosis in acute hospital settings. These findings informed the design of the phase IIa double-blinded randomised clinical trial SINAPPS2. The SINAPPS2 trial is investigating IVIG and rituximab versus placebo treatment without corticosteroids.

The SINAPPS2 trial tests the hypothesis that immunotherapy is an effective treatment for antibody-associated psychosis, either the first episode of psychosis or relapse following previous remission. The trial aims to show superiority of immunotherapy with IVIG and rituximab over conventional psychiatric care alone including antipsychotic therapy in patients with acute psychosis and central nervous system (CNS) membrane antibodies.

The trial was registered at ClinicalTrials.gov on 21 June 2017 (NCT03194815; https://clinicaltrials.gov/ct2/show/NCT03194815?term=NCT03194815&rank=1).

### Trial objectives

The primary objective is to test the efficacy of immunotherapy (IVIG and rituximab) in patients with acute psychosis associated with anti-neuronal membrane antibodies. The secondary objective is to test the safety of immunotherapy (IVIG and rituximab) in these patients.

## Methods

### Design

The SINAPPS2 trial is a phase IIa, double-blinded, multicentre randomised placebo controlled trial with 12 (up to 18 if required) months of follow-up. It will be conducted in five to eight acute National Health Service (NHS) hospital trusts across the UK with suitable facilities for treatment of this population.

### Participants

#### Inclusion criteria

Age 18–70 years.Acute psychosis symptoms for at least 2 weeks but not longer than 24 months in the current episode. Acute psychosis is defined as rating 4 or more for at least one of the following Positive and Negative Syndrome Scale (PANSS) [18] items: P1, delusions; P2, conceptual disorganisation; P3, hallucinatory behaviour; N1, blunted affect; N4, social withdrawal; N6, lack of spontaneity; G5, mannerisms/posturing; and G9, unusual thought content. This may be either a first episode or relapse after remission. Remission is defined as having mild or absent symptoms of psychosis for at least 6 months.Serum or cerebrospinal fluid (CSF) anti-neuronal membrane antibodies at pathological levels (including NMDAR, LGI1 and others, as determined by the Trial Steering Committee).Given informed consent by a patient or their legal representative.

#### Exclusion criteria

Duration of current episode of psychosis greater than 24 months.Co-existing severe neurological disease, including tumour, hippocampal sclerosis with refractory epilepsy, probable dementia with evidence of atrophy on brain imaging, moderate or severe learning disability, or any evidence of a current acute encephalopathy (for instance coma, seizures).Hepatitis B.Hepatitis C.Human immunodeficiency virus.IgG level < 3 g/L.Previous malignancy (unless agreed with Chief Investigator (CI)).Pregnant, breast feeding or inadequate contraception if female.Hypersensitivity or absolute contra-indication to any trial drug, murine proteins or excipients.Live vaccine within last 3 months.Previous treatment with rituximab in the past 12 months.Severe infection.Severe heart failure.Any other medical illness or disability that, in the opinion of the investigator, would compromise effective trial participation.Concurrent enrolment in another Clinical Trial of Investigational Medicinal Products (CTIMP).

### Treatment medication

The interventional treatments are intravenous immunoglobulin (IVIG) followed one month later by rituximab, given as two infusions a fortnight apart.

### Placebo

Patients receiving control treatment will receive matched placebo solutions for IVIG (human albumin solution 1%) and rituximab (NaCl 0.9%), with NaCl 0.9% being used in place of methylprednisolone pre-medication to maintain blinding.

### Route of administration and maximum dosage allowed

The overall duration of the treatment period for an individual participant will be approximately 50 days. The study medication will be used at standard clinical doses, and delivered as per local protocols. IVIG intravenous infusion of 2 g/kg (ideal body weight) will be given over 2–4 days as tolerated. Most participants are expected to receive the drug over two 2–6 h periods. Placebo (1% albumin solution) will be given over 2–4 days.

The IVIG dosage is weight determined (ideal body weight). Patients below 152.4 cm (5 ft) in height will be treated using their actual body weigh. IVIG dosing will be rounded down to the nearest 5 g regardless of the calculated dose; that is, if the calculated dose is 39.9 g, they will receive 35 g.

The two infusions of 1 g rituximab will be given 14 days apart, over 2–4 h as tolerated, with 100 mg methylprednisolone pre-medication to reduce infusion-associated adverse effects. The first infusion will commence at 50 mg/h; after the first 30 min, it may be escalated in 50 mg/h increments every 30 min, to a maximum of 400 mg/h. In the absence of serious previous infusion-related reactions, the second infusion can be infused at an initial rate of 100 mg/h and increased by 100 mg/h increments at 30-min intervals, to a maximum of 400 mg/h. The matching placebo solution (sodium chloride 0.9%) will be given in an equal volume and duration to that used for rituximab infusion. No dosage modifications are permitted.

The IVIG and matched placebo are provided by Biotest Ltd. Rituximab (or bio-similar), matching placebo and pre-medication will be supplied by local site pharmacies. Details on identity, supply, packaging, labelling, label design, prescriptions, dispensing and distribution of investigational medicinal products are described in the trial pharmacy manual.

### Concomitant therapy

All prescribed concomitant medications will be recorded monthly from screening to the end of study visit. Participants will continue with antipsychotic medications as standard of care, under the supervision of their local psychiatrist. Participants will not receive any other investigational medicinal products during the study period.

### Randomisation

An Internet-based system provided by Sealed Envelope will be used to randomise participants and allocate treatment to individual patients [19]. Eligible patients will be randomly assigned 1:1 to either the IVIG/rituximab group or the placebo group before the baseline assessment. Each group will contain approximately 40 participants. The randomisation will be performed using the minimisation technique of Pocock and Simon [20], using NMDAR (yes vs no), LGI1 (yes vs no), GABA-A (yes vs no), duration of psychotic illness (less than 12 weeks vs 12 weeks and longer) and current smoking status (currently smoking vs currently not smoking) as dichotomous minimisation factors.

Notification of treatment allocation will be forwarded to the central trial coordinator, local investigator and local pharmacy by email upon randomisation.

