### Method of blinding

Trial participants and investigators will be blinded to treatment allocation. Site pharmacies and other authorised delegates as required will be unblinded. Treatment products/pre-medication and the corresponding control will have identical presentations in product appearance, packaging and labelling.

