### Primary outcome measure

The Positive and Negative Syndrome Scale (PANSS) [18] is a clinician/researcher-rated 30-item scale for the assessment of the severity of symptoms of schizophrenia based on information obtained from a patient during the interview and from their family members and clinicians. Each item is rated from 1 (absent) to 7 (extreme) and they are grouped into three subscales: Positive Scale, P (7 items); Negative Scale, N (7 items); and General Psychopathology Scale, G (16 items). The sum of individual ratings within each subscale gives score ranges of 7–49 for the Positive Scale and Negative Scale and of 16–112 for the General Pathology Scale. A higher score indicates severe symptoms.

The primary outcome will be assessed by eight selected PANSS items [21]. These include three Positive Scale items (P1, delusions; P2, conceptual disorganisation; P3, hallucinatory behaviour), three Negative Scale items (N1, blunted affect; N4, passive/apathetic social withdrawal; N6, lack of spontaneity) and two items from the General Pathology Scale (G5, mannerisms/posturing; G9, unusual thought content).

PANSS assessments will be conducted by trained researchers. Their training includes PANSS training by certified trainers followed by observed role-play interviews with feedback, observed mock interviews with non-patients and patients with psychosis, and mock-interview videoing and analysis. Thereafter, there will be periodical refresher training with certified PANSS trainers and researchers’ independent rating of individual patient video interviews over the trial period.

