### Screening, baseline, treatment and follow-up

#### Outline

Screening assessments and procedures, summarised in Fig. 1, will only be conducted after a participant has signed the consent form. Participants will be randomised after confirmation of their eligibility, and before the baseline visit. The eligibility must be confirmed within a maximum of 2 months from the informed consent. There is no other time limit for randomisation. The baseline visit will be scheduled a maximum of 4 weeks after confirmation of eligibility and a maximum of 7 days before IVIG/placebo treatment. Rituximab first infusion will follow after 4–5 weeks and rituximab second infusion 2–3 weeks later. All trial participants will be required to attend follow-up clinical visits at 3, 6, 9 and 12 months, which will be an end of study visit. Participants may need to be followed for longer and attend a clinical visit at month 15 and 18 if the primary outcome data need to be obtained beyond month 12. In addition, a monthly follow-up brief telephone or visit assessment will be administered by researchers. Anonymised data will be transferred in Case Report Forms (CRFs) by the trial researchers and clinicians. All CRFs will be completed in the manner, and within the timelines, detailed in the CRF-completion guidelines and sent to the trial coordinator at the Cambridge Clinical Trials Unit (CCTU). The CRFs will be accessible to trial coordinators, data managers, the investigators, clinical trial monitors, auditors and inspectors as required. All trial data will be entered and stored in a MACRO database. A trial-specific data management plan will describe in detail the data management processes.Screening visit and Assessments (Visit 1)

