### Withdrawal

Patients who have withdrawn from the allocated treatment will remain in the trial and be followed up as set out in the protocol, unless they withdraw their consent for this trial. Any data and samples collected up until that point of consent withdrawal will continue to be used in the trial. However, no further information will be collected or tests performed. Participants who withdraw between randomisation and treatment will be replaced.

In addition, participants must be withdrawn from their allocated treatment arm if they develop severe encephalopathy (e.g. typical of NMDAR encephalitis or LGI1-antibody encephalopathy), which would necessitate withdrawal to facilitate best standard of care of management for these conditions [7]; the participant develops severe reactions to the Investigational Medicinal Products (IMP) (e.g. anaphylaxis to first rituximab infusion, aseptic meningitis to first dose of IVIG); or a female participant becomes pregnant or will no longer use contraception.

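### The Randomisation section sends the treatment allocation to the local investigator, whom the blinding section says is kept blind

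*Protocol article*

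**What the plan says.** Four parts of the protocol article bear on who knows the arm.

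- **Randomisation:** "Notification of treatment allocation will be forwarded to the central trial coordinator, local investigator and local pharmacy by email upon randomisation". One sentence covers all three recipients and draws no distinction in what each receives.
- **Method of blinding:** "Trial participants and investigators will be blinded to treatment allocation", followed by "Site pharmacies and other authorised delegates as required will be unblinded".
- **Design:** "The SINAPPS2 trial is a phase IIa, double-blinded, multicentre randomised placebo controlled trial".
- **Emergency unblinding:** when an adverse event makes the arm relevant to management, the treating physician may obtain it from the web randomisation system, and must document and explain this to the sponsor.

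On timing, the Outline section says: "Participants will be randomised after confirmation of their eligibility, and before the baseline visit". On pre-treatment losses, the Withdrawal section says: "Participants who withdraw between randomisation and treatment will be replaced".

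On measurement, the Primary outcome measure section says that the PANSS "is a clinician/researcher-rated 30-item scale for the assessment of the severity of symptoms of schizophrenia", and that "PANSS assessments will be conducted by trained researchers".

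**The concern.** The item sent to the investigator in one section is the item withheld from the investigator in the next. A site or trials unit that followed the Randomisation section to the letter would unblind every local investigator at the moment of randomisation.

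This matters more here than it would with a laboratory or mortality endpoint. Remission requires all eight selected PANSS items to score 3 or less, so a one-point difference in judgement on a single item, between 3 and 4, changes a participant's status. Knowledge of the arm at the site could also influence who leaves between randomisation and the first infusion. Those participants are replaced, and the primary analysis is per protocol, limited to participants who received all trial drugs and had no major violation. Selective early losses would therefore not be counted in the primary comparison.

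**Working it through.** No figure in the plan bears on this point, and the sample size does not depend on it. The check is a comparison of the sections.

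1. **Same object.** Randomisation and Method of blinding both refer to the treatment allocation. Neither distinguishes a masked form (a kit or randomisation number) from the arm itself.

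2. **Can the investigator be one of the authorised delegates?** Not on the text. The sentence just before the one about delegates puts investigators, as a class, on the blinded side.

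3. **Does the text suggest a masked email?** No. The pharmacy must know the arm to prepare the infusions, and it appears in the same list, in the same terms, as the investigator.

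4. **Does another section settle it?** Emergency unblinding supports the blinded reading, since a physician who had already been told the arm would not need the procedure. This shows what was intended, but it leaves the Randomisation sentence in conflict with two other sections.

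5. **When would the arm be known?** Randomisation comes after eligibility is confirmed and before baseline. Baseline may be up to 4 weeks after that confirmation, and the first infusion up to 7 days after baseline. The notice could therefore precede treatment by up to 28 + 7 = 35 days. It would precede the baseline PANSS and all follow-up, which lasts 12 months and up to 18 if required.

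6. **Who would know, by role?**

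| Role | Named recipient of the email? | Stated blinding status |
|---|---|---|
| Local investigator | Yes | Blinded |
| Central trial coordinator | Yes | Not stated; could be an authorised delegate |
| Site pharmacy | Yes | Unblinded |
| Trained researchers rating PANSS | No | No separate statement |
| Local psychiatrist supervising antipsychotics | No | No separate statement |

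The direct contradiction is confined to the first row. For the coordinator the article leaves the status open. That role receives the case report forms and sits with the principal investigators in a management group that meets weekly, so its status should be stated. For raters, exposure would be indirect, through the site team.

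7. **Which outcomes would be touched?** The primary outcome is an absolute threshold and does not use the baseline score. The exposed part is the follow-up rating, together with pre-treatment withdrawal. A baseline rating made with knowledge of the arm could affect the secondary outcome of percentage reduction in PANSS total, if that is measured from baseline.

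**The case against.** The strongest reply is that this is loose wording in a condensed article. Notifying an allocation can mean sending a masked confirmation, the blinding section is explicit, and the emergency procedure makes sense only if physicians are blind. The article also refers to a trial or randomisation system manual, not shown, where notification settings would normally be found. This stands as far as it goes: the text does not establish that the blind was broken. It does not remove the conflict, because the article positively states who receives the allocation rather than leaving it to another document.

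A reader might infer more, in five ways that the documents do not support.

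- **That the raters or treating psychiatrists are unblinded.** Neither is a named recipient.
- **That the coordinator's receipt of the email is itself a contradiction.** That role is not listed as blinded.
- **That known past allocations make the next minimised allocation predictable.** Nothing says a local investigator sees other sites' allocations or covariates, and site is not a minimisation factor.
- **That randomisation must be moved after baseline.** The order is stated consistently. Once the notice is masked, most of the reason to change it disappears.
- **That the bias can be quantified.** Suppose there is no true effect, recovery is 35% in both arms, and biased rating moves it to 40% v 30%. Then HR = ln(0.60)/ln(0.70) = 1.43; events = 28 × (0.40 + 0.30) = 19.6; shift = √(19.6/4) × ln(1.43) = 0.80; and P(Z > 1.645 − 0.80) ≈ 0.20 against a nominal 0.05. The arithmetic is right, but both the shift and the common 35% are assumptions, and any other shift would give another answer.

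**Conclusion.** The notification rule is wrong as written. It contradicts the blinding section for the local investigator and is inconsistent with the emergency unblinding procedure. If executed literally, it would defeat the double blind at the investigator level from before baseline onwards. It would also put the rated primary outcome and pre-treatment withdrawal at risk of bias through the site team. That conclusion rests on one assumption: that the email carries the arm to every recipient, as the sentence reads. If the investigator's copy in fact carries only a code, the fault is in the wording alone. The size of any bias cannot be computed from the documents.

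**What to change.** Amend the Randomisation section to state what each recipient gets:

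- the unmasked allocation goes only to the site pharmacy and to named unblinded delegates;
- the local investigator receives a masked confirmation with a randomisation number only;
- the central coordinator receives the same masked confirmation, unless that role is expressly named as an unblinded delegate.

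Add to Method of blinding that PANSS raters are blinded to allocation.

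For participants already enrolled (seven at submission), check what the emails contained and who received them, and report any unblinding found. A sensitivity analysis that drops affected assessments is not a useful remedy: if the notices were unmasked, it would exclude every participant randomised under them.

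The cost is one protocol sentence for the notice, a statement on raters, and a check of the notification setting in the web randomisation system. Visit timing and pharmacy notice need not change.
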